### Secondary Analyses

This study is an observational audit with an embedded cluster randomized design and was planned so that the following factors could be analyzed for association with TURBT quality indicator achievement and early recurrence rate: (1) surgeon factors: (a) the experience of the operating surgeon in years, (b) total number of cases performed by the surgeon to date, (c) number of cases performed per month on average in the last year, and (d) a self-declared specialist interest in bladder cancer; (2) TURBT surgery performed on a dedicated TURBT list; (3) the estimated annual TURBT case volume of the site; (4) the use of en-bloc resection; (5) the use of diagnostic visual aids including: (a) photodynamic diagnosis–assisted resection, (b) narrow band imaging, and (c) Storz Professional Image Enhancement System; (6) the length of inpatient stay; (7) geographical region—continent; (8) World Health Organization health care quality and access index for the country; (9) the preexistence of a TURBT audit at the site; (10) the use of re-TURBT; (11) the use of primary adjuvant BCG or Mitomycin C; and (12) patient factors: age and sex.

## Discussion

This study aims to use a distributed collaborative model to deliver a site-level web-based performance feedback intervention to improve the quality of endoscopic bladder cancer surgery. The goal is to gain incremental benefit across vast numbers of patients using a simple and cheap intervention that will amount to large absolute benefits across the population of patients with NMIBC. We have considered previous advice from systematic reviews of previous audit and feedback interventions and used the theoretical domains framework to design the feedback intervention. We have worked closely with expert international clinical, methodological, and statistical professionals to ensure quality of study design.

The effectiveness of audit and feedback in improving professional practice varies depending on “baseline performance and how feedback is provided” as well as setting [16]. We have determined that a clinically relevant relative difference between intervention and control arms is 10% and powered this study accordingly. Electronic audit and feedback have also been found to have variable effectiveness, and a systematic review recommended closer attention to theoretical domains targeted [21]. We have done this as part of the study design. This study is unique because of its global multicenter reach and therefore aspires to power a cluster-cluster randomized controlled study design to confidently determine the effect of the intervention. The Hawthorne effect will be accounted for since we measure performance retrospectively (when the study was not known about) and then compare 2 parallel arms in the randomized study. There have been previous time-series studies of audit and feedback in TURBT surgery, which suffer from the lack of a contemporaneous control group [15,40]. To our knowledge, this will be the first randomized study of audit and feedback in TURBT surgery. Limitations of the study design include the pragmatic intervention—clinicians can choose to engage or not, and implementation at the site level is left up to local teams. The site-level intervention and analysis will limit the ability to make conclusions about the behavior of individuals. In conclusion, this study will determine if audit, feedback, and education is effective in improving professional practice in the quality of TURBT surgery and if this reduces NMIBC early recurrence rates.

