### Sample Size

The intervention will be delivered to centers, and so the primary outcomes will also be measured at the center level. The only published data about intersite achievement of the listed coprimary outcomes are the Scottish Quality Performance Indicator programme covering 11 sites in Scotland. The outcome with the largest SD (SI-IVC) was used to determine the overall sample size. With mean 0.651 (SD 0.2) for SI-IVC, recruiting 172 sites (86 per arm) would give 90% power to detect a difference of 0.1 between the intervention and control groups at the 5% significance level. Where a smaller SD of 0.1 (detrusor muscle in specimen) or 0.15 (resection documenting) can be assumed, this would provide 90% power at the 5% significance level to detect differences of 0.05 and 0.075, respectively. It is possible that some sites may have missing data for 1 or more of the coprimary outcomes. Missing data will not be imputed for the primary outcomes. In that case, the site will be excluded from the analysis for that outcome. A sensitivity analysis will be performed to determine the effect of missing data in that outcome. An extensive international marketing campaign will be undertaken to ensure sample size is reached, along with endorsement of the study by the British Association of Urological Surgeons to all urology centers in the United Kingdom.

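### The Discussion says the trial is powered for a 10% relative difference, but the sample size was set on 0.1 absolute in SI-IVC, which is 15.4% relative on the stated mean

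*Protocol article*

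**What the plan says.** Two sections of the protocol article describe the target difference.

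- **Sample Size.** The trial is sized on SI-IVC, chosen because it has the largest SD of the indicators considered: "With mean 0.651 (SD 0.2) for SI-IVC, recruiting 172 sites (86 per arm) would give 90% power to detect a difference of 0.1". The test level given there is 5%. The same section adds that, at 90% power, a difference of 0.05 could be detected if the SD is 0.1 (detrusor muscle) and 0.075 if the SD is 0.15 (resection documenting). It gives no means for these two, and neither an SD nor a difference for the tumor-features indicator.
- **Discussion.** "We have determined that a clinically relevant relative difference between intervention and control arms is 10% and powered this study accordingly".

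The Analysis section defines each primary outcome as a site-level proportion, treats it as continuous, and fits a mixed effects linear regression with baseline achievement of the same indicator as a fixed effect. The estimated arm effect is therefore a difference in proportions. No section links the relative figure in the Discussion to the absolute figure in Sample Size.

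**The concern.** On a proportion with mean 0.651, 0.1 absolute and 10% relative are different targets, and the second is about a third smaller. The Discussion calls the smaller one clinically relevant and says the study was sized for it. The calculation was done for the larger one.

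The target difference is what a reader uses to judge a null result. Anyone who takes the Discussion at its word could read a non-significant SI-IVC result as good evidence, at 90% power, against a 10% relative improvement. On the planning figures the design does not carry that much information about an effect of that size. The protocol does not say it will read null results this way; the risk comes from the wording.

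**Working it through.** **Inputs.** All are from Sample Size except the last two.

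- SI-IVC mean 0.651, SD 0.2: "With mean 0.651 (SD 0.2) for SI-IVC"
- Sites: "recruiting 172 sites (86 per arm")
- Difference and power: "90% power to detect a difference of 0.1 between the intervention and control groups"
- Significance level 5%. The sidedness is not stated; step 1 tests it.
- Claimed target of 10% relative, from the Discussion.
- Baseline achievement as a covariate, from Analysis. No correlation is given, so a range is assumed below.

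**Step 1. Reproduce the plan's figure.** For two means, n per arm = 2 (z₁₋α/₂ + z₁₋β)² SD² / δ².

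With two-sided 5%, 90% power, SD 0.2 and δ = 0.1: n = 2 × (1.960 + 1.282)² × 0.04 / 0.01 ≈ 84.1, so 85 per arm. The t-test version gives 85.03, so 86 per arm and 172 in total, as stated. Power at 86 per arm is 90.6% (normal) or 90.3% (t). A one-sided 5% test would need only 69 per arm, so the plan's figure implies a two-sided test and 0.1 on the absolute scale. The pairs 0.05 with SD 0.1 and 0.075 with SD 0.15 have the same standardized difference of 0.5, and therefore the same power.

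**Step 2. Put both targets on one scale.**

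- 0.1 / 0.651 = 15.4% relative
- 10% × 0.651 = 0.0651 absolute

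**Step 3. Power for 10% relative on SI-IVC, unadjusted.**

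- Standard error of the difference = 0.2 × √(2/86) = 0.0305
- 0.0651 / 0.0305 = 2.134
- Power ≈ Φ(2.134 − 1.960) = 56.9% (normal), or 56.5% (t)

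For 90% power at 0.0651, 199 (normal) to 200 (t) sites per arm would be needed, against 86. This takes 0.651 as the control mean. If it were the midpoint of the two arms or the intervention mean, power would be about 53% or 49%.

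**Step 4. Allow for baseline adjustment.** With correlation r between baseline and follow-up site proportions, the residual SD is 0.2 × √(1 − r²). The values of r are assumptions.

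| r | residual SD | power for 0.0651 (t / normal) |
|---|---|---|
| 0 | 0.200 | 56% / 57% |
| 0.3 | 0.191 | 60% / 61% |
| 0.5 | 0.173 | 69% / 69% |
| 0.7 | 0.143 | 84% / 85% |
| 0.76 | 0.130 | 90% / 91% |
| 0.8 | 0.120 | 94% / 94% |

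Power reaches 90% at r of about 0.75 (normal) to 0.76 (t).

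**Step 5. Other indicators.** A 10% relative difference is 0.1 × mean, and the means are not given. Over assumed means of 0.5 to 0.9, unadjusted power would be about 91% to over 99% at SD 0.1, and about 59% to 98% at SD 0.15. No single figure can be fixed from the protocol.

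**The case against.** The strongest reply is that the word relative in the Discussion is a slip. The Discussion says 10% and Sample Size uses 0.1, the same number on the proportion scale, and the planned linear model estimates an absolute difference. On that reading the trial has the power it claims, nothing in the design changes, and one word is wrong. This is plausible and the documents do not rule it out. It does not remove the point, because the published statement of the clinically relevant difference would then itself be wrong and need correcting.

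A second reply is that the planned baseline adjustment will recover the power. That stands in part. With a strong enough correlation (about 0.76 or more) power for 0.0651 reaches 90%, so it would be wrong to say that adjustment must fall short. But the stated calculation takes no credit for adjustment, and the protocol gives nothing from which to judge the correlation.

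A third reply is that the abstract reports 220 participating hospitals. Hospitals and clusters need not coincide, since a cluster may contain several hospitals. Even if all 220 counted as separate sites, 110 per arm would give about 67% unadjusted power (67.5% normal, 67.1% t).

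A reader might also set the 4.3% median audit-and-feedback improvement cited in the Introduction against the SI-IVC planning figures and conclude that power for it is very low. The protocol does not say that this 4.3% is in percentage points, and it is a baseline-adjusted figure that does not belong with an unadjusted SD. It has no bearing on this point.

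**Conclusion.** The Discussion and Sample Size sections contradict each other on the target difference and must be reconciled. The trial was sized for 10 percentage points absolute in SI-IVC, about 15% relative, and not for 10% relative. If 10% relative is the intended clinically relevant difference, unadjusted power for SI-IVC is about 56-57%. That figure assumes 86 sites per arm, SD 0.2, a two-sided 5% test and 0.651 as the control mean.

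Three stronger conclusions might be inferred, and the documents support none of them:

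- That the 90% in Sample Size is a miscalculation. It reproduces, and it is correct for the difference it names.
- That the trial as a whole is underpowered. The shortfall is conditional on 10% relative being meant, and it is shown only for SI-IVC, the outcome that set the sample size.
- That more sites are required. The 199 to 200 per arm in the working shows how far apart the two targets are; it is not a recommendation.

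**What to change.** Reword the Discussion sentence to say that the trial was sized to detect a 10 percentage point absolute difference in the site-level SI-IVC proportion, about 15% relative to the planning mean of 0.651. Give 0.05 (SD 0.1, detrusor muscle) and 0.075 (SD 0.15, resection documenting) as differences detectable at 90% power if those SDs hold. They should not be presented as targets that set the sample size, and 0.075 should not be extended to the tumor-features indicator, for which Sample Size gives no SD.

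If 10% relative is the clinically relevant difference intended, keep it, remove the claim that the study was powered for it, and state the SI-IVC power: about 56% unadjusted, or a higher figure with the assumed baseline correlation shown.

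In either case, interpret a null SI-IVC result by its confidence interval against the stated target.

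The cost is a sentence of wording and, at most, one restated power figure. The number of sites, the analysis model and the decision rule do not change.

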## Abbreviations

APEASE: Affordability, Practicability, Effectiveness and Cost-effectiveness, Affordability, Side-effects, Equity
AUA: American Urological Association
BCT: behavior change technique
CHaRT: Centre for Healthcare Randomised Trials
EAU: European Association of Urology
EORTC: European Organisation for Research and Treatment of Cancer
NICE: National Institute for Health and Care Excellence
NMIBC: nonmuscle invasive bladder cancer
REDCap: Research Electronic Data Capture
SI-IVC: single-instillation intravesical chemotherapy
TURBT: transurethral resection of bladder tumor
